#### Data collection and management

To improve the workflow, patient data are collected via the customized EHR, which only collects information necessary for hypertension pharmacological management (Table 3). The EHR performs built-in data checks to verify that the data are complete and meet predefined data ranges and formats. Blood pressure is measured with a validated automated sphygmomanometer (Omron HBP-1300) [22], after at least a 5-min rest in the sitting position. Two blood pressure readings are taken 1–2 min apart, and the average value is recorded. Trained primary care doctors (with the assistance of other trained providers at some sites) are responsible for participant enrolment and follow-up. After enrolment, eligible participants are asked to attend the clinic at least every 3 months for follow-up. As we include participants registered for hypertension treatment at the primary care site in this trial, a substantial proportion of them are expected to be retained. To maximize the retention of participants, they will also be contacted and invited to attend the clinics for collecting data during follow-up.

**Table 3 Tab3:** Data elements collected in baseline, recruitment, and follow-up

	Baseline	Recruitment	Follow-up
Socio-demographics (age, gender, education, and insurance)	√	√	√
Physical measurements (blood pressure, heart rate, waist, height, and weight)	√	√	√
Self-reported home monitoring blood pressure		√	√
Cardiovascular risk factors	√	√	√
Comorbidities	√	√	√
Hospitalizations		√	√
Adverse events		√	√
Current medications	√	√	√
Medication adherence^a^	√	√	√
Side-effects related to antihypertensive medication		√	√
CDSS recommendations^b^		√	√
Prescriptions	√	√	√
Reasons for not following CDSS^b^		√	√

^**a**^ Adherence to each antihypertensive medication is collected as three classes: regularly, intermittently, and rarely

^b^ Only in the intervention sites of the LIGHT trial

All data are securely transmitted to the central server through automatic electronic transfer and securely stored in an encrypted and password-protected database. Data confidentiality policies on data collection, storage, and analysis have been strictly imposed to ensure the confidentiality of personal information.

#### Data monitoring and quality control

The Trial Steering Committee periodically reviews trial progress and provides advice to the investigators on all aspects of the trial. No interim analyses of intervention effectiveness are planned. Due to the low-risk nature of the trial, a Data Monitoring Committee is not necessary. Similarly, there are no anticipated adverse events and harms from the trial intervention. Any unanticipated problems and adverse events will be reported to the research team and appropriate regulatory bodies.

We randomly select blood pressure values recorded in EHR daily (at least one value per site) and check against the recordings in the automated sphygmomanometer. We also compare the prescription recorded in the EHR with paper/electronic prescription sheets to verify their consistency biweekly. A bespoke website was developed for the research team to monitor the progress and quality of the trial in real time. Through this website, we can review the comparison results of blood pressure values in EHR and sphygmomanometer to monitor the accuracy of documentation in all sites, and any data with invalid values can be searched and traceable corrected. CDSS recommendations can be also viewed via the website to ensure that the CDSS is working as designed. In addition, on-site audits are regularly conducted by the research team to verify that data are generated, documented, and reported in compliance with the protocol.

#### Sample size

As this is a staged pragmatic trial, we have the capacity to add sites as the trial progresses. Initial statistical power was based on the number of sites potentially eligible in stage 1 at the time the power analysis was being conducted; thus, we assumed that at least 10 primary care sites would be randomized to the intervention arm and 10 to the control arm, the baseline appropriate treatment rate would be 55% with maximum type I error of α = 0.05, a moderate intra-site correlation of 0.05, a within-patient correlation of 0.1, and statistical power of 90%, and we needed 3 hypertension visits per patient for 50 patients at each site to detect an 18% absolute difference in the appropriate treatment rate between the two arms. Subsequent enrolment increased the number of participating sites to 94, randomized in 4 stages; under the same assumptions as above, we anticipate that the final sample will provide 90% power to detect a true difference of 4% in the appropriate treatment rate. This difference is close to the average effect of CDSS in improving the process of care in prior studies [23, 24].

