#### Statistical analysis

The analyses and reporting of the results will follow the Consolidated Standards of Reporting Trials guidelines for cluster-randomized controlled trials [25]. All the analyses will be performed on an intention-to-treat basis. Multiple imputations by chained equations will be used to account for missing values.

With all comparative outcomes, we will use mixed-effects generalized linear regression models, using logistic or linear response for dichotomous or continuous outcomes, respectively, and including a random effect for the study site. Implementation stages will be treated as strata, with adjustment for calendar time to account for secular trends. The consistency of treatment effects on the primary outcome will be explored in predefined subgroups, including age, gender, education, implementation stage, tertiles of baseline cluster-level appropriate treatment rate, blood pressure level, and use of antihypertensive medications. All statistical tests will be performed using 2-sided tests at the 0.05 level of significance, but the number of tests and *p*-value will be taken into account in the interpretation of the results.

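### With 94 sites and the stated assumptions, the LIGHT trial has 90% power for a difference of about 8 points, not 4; power for 4 points is about 37%.

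*Protocol article*

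**What the plan says.** The Sample size section for the LIGHT trial starts from 10 sites per arm. It assumes that "the baseline appropriate treatment rate would be 55% with maximum type I error of α = 0.05", with "a moderate intra-site correlation of 0.05, a within-patient correlation of 0.1", and 3 visits from each of 50 patients per site. On these inputs it gives 90% power for an absolute difference of 18 points in the appropriate treatment rate, the primary outcome.

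It then reports that the number of sites has grown to 94, states that the assumptions are the same, and concludes: "we anticipate that the final sample will provide 90% power to detect a true difference of 4% in the appropriate treatment rate". It adds: "This difference is close to the average effect of CDSS in improving the process of care in prior studies".

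The Allocation section gives 1:1 randomization of sites. The Statistical analysis section says: "All statistical tests will be performed using 2-sided tests at the 0.05 level of significance".

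**The concern.** The two power statements stand next to each other and differ only in the number of sites. Multiplying the sites by 94/20 = 4.7 should divide the detectable difference by √4.7 = 2.17. The article divides it by 18/4 = 4.5. Both figures therefore cannot be right on one set of assumptions.

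This is the headline power claim for the primary outcome, and the article uses it to suggest that the trial can detect an effect of the size usually seen with decision support. If true power at that size is far below 90%, a non-significant result would say little about whether such an effect exists. A reader relying on the printed figure could take it as evidence against one.

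**Working it through.** **Inputs.** From Sample size: rate 55%, α = 0.05, power 90%, intra-site correlation ρ = 0.05, within-patient correlation 0.1, m = 50 patients per site, 3 visits each, k = 10 and later 94/2 = 47 sites per arm. From Statistical analysis: two-sided tests. From Trial status: 7,656 patients in 94 sites, about 81 per site.

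**Step 1: scaling, with no design-effect formula.** With m and the correlations fixed, the detectable difference is proportional to 1/√k.

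- From 18 points at 20 sites: 18 × √(20/94) = 8.3 points at 94 sites.
- Going from 18 to 4 points would take 20 × (18/4)² = 405 sites.

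**Step 2: the 20-site figure.** The variance of a site's mean, in units of p(1 − p), is

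ρ + (0.1 − ρ)/m + (1 − 0.1)/(3m) = 0.05 + 0.001 + 0.006 = 0.057.

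Multiplied by 150 visits, this is a design effect of 8.55. With p(1 − p) = 0.55 × 0.45 = 0.2475 in both arms,

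SE = √(2 × 0.2475 × 0.057/10) = 0.0531.

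The detectable difference at 90% power is (1.960 + 1.282) × 0.0531 = 17.2 points with normal quantiles, or 18.2 with a t distribution on 18 df. Using the intervention arm's own variance instead gives 16.4 to 17.3 points. The stated 18 points is thus approximately reproduced.

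**Step 3: the 94-site figure by the same method.** SE = √(2 × 0.2475 × 0.057/47) = 0.0245. The detectable difference is 3.242 × 0.0245 = 7.9 points (8.0 with t; 7.8 to 7.9 with the intervention arm's own variance). Power for 4 points is Φ(0.04/0.0245 − 1.960) = Φ(−0.33) = 37%.

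**Step 4: can enrolment close the gap?**

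| Patients per site (47 sites per arm) | Detectable difference, 90% power | Power for 4 points |
|---|---|---|
| 50 | 7.8 to 8.0 points | about 37% |
| 81 (7,656/94) | 7.6 to 7.8 points | 38% to 39% |
| Unlimited | 7.3 to 7.5 points | 41% to 42% |

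Once ρ = 0.05 is fixed, the between-site term sets a floor that neither patients nor visits can lower.

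**Step 5: what would 4 points require?** Setting 3.242 × SE = 0.04 gives a variance factor of (0.04/3.242)² × 47/0.495 = 0.0145, against 0.057. That is about 75% less variance. The corresponding intra-site correlation is about 0.007 with 50 patients per site and about 0.010 with 81, five to eight times below the assumed 0.05. Keeping ρ = 0.05 and 50 patients per site, about 184 sites per arm would be needed.

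**Step 6: other readings of the inputs** (94 sites, 50 × 3 visits).

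- Adding the patient correlation to the site correlation (design effect 8.65): 7.9 to 8.0 points, 37% power for 4 points.
- One-sided test: 7.1 points, 50%. This contradicts the stated two-sided testing.
- Multiplying the two design effects (1.2 × 3.45 = 4.14): 5.5 points, 66%.
- Applying the site design effect to patients only (3.45): 5.0 points, 73%, or 83% if also one-sided.

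The last two design effects, tested two-sided, put the 20-site figure at 11 to 12 points, so they do not match the stated 18. No reading that keeps ρ = 0.05 reaches 90% power for 4 points.

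**The case against.** The arithmetic was not disputed. The fair objections concern how much rests on it.

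- **Stratification and adjustment.** Sites are stratified by baseline appropriate treatment rate and site characteristics, and the analysis treats stages as strata and adjusts for calendar time. These steps may reduce between-site variance, so actual power could exceed 37%. This stands as a caution: the 37% is conditional on ρ = 0.05 with no such gain. It does not rescue the printed figure, because about three quarters of the variance would have to go. The section claims no gain and says the assumptions are unchanged.
- **The 20-site match is approximate.** It runs from 16.4 to 18.2 points depending on the variance and the reference distribution. That is true, but the 94-site result moves only between 7.8 and 8.0 points, and the scaling in Step 1 takes the stated 18 points as given.
- **Source of the error.** Linear scaling, 18 × 20/94 = 3.8, falls near the stated 4. The article does not show its working, so this is only a numerical coincidence worth checking.
- **Interpretation of a null result.** The article does not say how one would be read. The risk of misreading is an inference from the sentence on prior studies, not a statement in the plan.
- **Seriousness.** All 94 sites are already randomized, and the error alters no allocation, model or error rate. That is why the remedy is confined to wording. The stated power for the primary outcome is still wrong.

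**Conclusion.** The concern holds. On the article's own inputs, 47 sites per arm give 90% power for about 8 points and about 37% power for 4 points, against the 90% stated. A true 4-point benefit would be missed in nearly two trials out of three. This rests on a 55% control rate, an intra-site correlation of 0.05, two-sided testing at 0.05, equal site sizes and no variance reduction from stratification or covariates. Within those assumptions the conclusion does not depend on the number of patients per site. The error concerns the trial's stated sensitivity, not the validity of the primary test.

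**What to change.** In the Sample size section for the LIGHT trial:

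1. Replace the 4% figure with about 8 points at 90% power, and state that power for a 4-point difference is about 37% at an intra-site correlation of 0.05.
2. Delete or reword the sentence that places the detectable difference close to the average effect in earlier studies.
3. Add a sentence that a non-significant result will be read through its confidence interval and will not be taken to rule out a 4-point effect.
4. If the 4% came from a smaller correlation or from an allowance for stratification or covariates, state that input and withdraw the claim that the assumptions are unchanged.

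The cost is wording only, although the stated power becomes less favourable. No extra sites, patients or analyses are requested.

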#### Statistical analysis

The analyses and reporting of the results will follow the Consolidated Standards of Reporting Trials guidelines for cluster-randomized controlled trials [25]. All the analyses will be performed on an intention-to-treat basis. Multiple imputations by chained equations will be used to account for missing values.

With all comparative outcomes, we will use mixed-effects generalized linear regression models, using logistic or linear response for dichotomous or continuous outcomes, respectively, and including a random effect for the study site. Implementation stages will be treated as strata, with adjustment for calendar time to account for secular trends. The consistency of treatment effects on the primary outcome will be explored in predefined subgroups, including age, gender, education, implementation stage, tertiles of baseline cluster-level appropriate treatment rate, blood pressure level, and use of antihypertensive medications. All statistical tests will be performed using 2-sided tests at the 0.05 level of significance, but the number of tests and *p*-value will be taken into account in the interpretation of the results.

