**Methods:**

The Learning Implementation of Guideline-based decision support system for Hypertension Treatment (LIGHT) trial is a pragmatic, four-stage, cluster-randomized trial conducted in 94 primary care sites in China. For each city-based stage, sites are randomly assigned to either implementation of the CDSS for hypertension management (which guides doctors’ treatment recommendations based on measured blood pressure and patient characteristics), or usual care. Patients are enrolled during the first 3 months after site randomization and followed for 9 months. The primary outcome is the proportion of hypertension management visits at which guideline-based treatment is provided.

In a nested trial conducted within the CDSS, with the patient as the unit of randomization, the LIGHT-ACD trial, patients are randomized to receive different initial mono- or dual-antihypertensive therapy. The primary outcome of the LIGHT-ACD trial is the changes in blood pressure.

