#### Outcomes

The primary outcome for the LIGHT trial is the proportion of hypertension visits (see Supplement 2 for specification) during which appropriate antihypertensive treatment is prescribed. Appropriate antihypertensive treatment is defined as a prescription compliant with the pre-specified guideline-based recommendations (see Supplement 4 for specifications). The secondary outcomes include the average change in systolic blood pressure, the proportion of those whose blood pressure is controlled at 9 months, and the proportion of hypertension visits with *acceptable* antihypertensive treatment, which is defined as either appropriate antihypertensive treatment (as above) or those treatments with acceptable reasons for failing to titrate antihypertensive treatment. An exploratory outcome is the number of patients experiencing a vascular event defined as a composite of cardiac death, non-fatal stroke, and non-fatal myocardial infarction (Table 2).

**Table 2 Tab2:** Outcomes of LIGHT and LIGHT-ACD trials

Outcomes	LIGHT	LIGHT-ACD
**Primary**	Appropriate (guideline-based) antihypertensive treatment rate	Absolute change in blood pressure at 9 months of different regimens of initial therapy
**Secondary**	Absolute change of systolic blood pressure at 9 months	Proportion of individuals with blood pressure controlled (SBP <140 mmHg and DBP <90 mmHg) at 9 months
	Blood pressure control rate (defined as SBP <140 mmHg and DBP <90 mmHg) at 9 months	Proportion of individuals with SBP <160 mmHg and DBP <100 mmHg at 9 months
	Acceptable (appropriate/non-appropriate but with proper reasons) antihypertensive treatment rate	Proportion of individuals who received monotherapy^a^, dual therapy, triple therapy, and referral at 9 months
		Proportion of individuals with antihypertensive drug side-effects
		Proportion of individuals transferred to usual care for any reason
**Exploratory**	A composite of cardiac death, non-fatal stroke, and non-fatal myocardial infarction	Absolute change in blood pressure at 9 months of different protocols^a^

Primary and secondary outcomes of LIGHT-ACD were assessed among initiating therapies; exploratory outcomes of LIGHT-ACD were assessed among protocols

*SBP* systolic blood pressure, *DBP* diastolic blood pressure

^a^ Only assessed in Population 1, who are not currently taking any antihypertensive medication with systolic blood pressure 140–159 mmHg, and initiated with monotherapy

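### The stated LIGHT model names a site random effect but no term for repeated visits within patients; fitted as written, exploratory patient-level subgroup tests would be mildly anti-conservative

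*Protocol article*

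**What the plan says.** All references are to the LIGHT part of the protocol article, apart from one sentence in the abstract.

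- **Outcomes.** The primary outcome is "the proportion of hypertension visits (see Supplement 2 for specification) during which appropriate antihypertensive treatment is prescribed". The unit is the visit, and the response is binary.
- **Abstract (Methods) and Data collection and management.** "Patients are enrolled during the first 3 months after site randomization and followed for 9 months", and "eligible participants are asked to attend the clinic at least every 3 months for follow-up". Each patient therefore contributes repeated binary responses.
- **Sample size.** The stage 1 calculation states that "we needed 3 hypertension visits per patient for 50 patients at each site". It assumes an intra-site correlation of 0.05 and, separately, "a within-patient correlation of 0.1".
- **Statistical analysis.** "With all comparative outcomes, we will use mixed-effects generalized linear regression models", with a logistic form for dichotomous outcomes, "including a random effect for the study site". No patient random effect, within-patient correlation structure or robust variance is named.
- **Statistical analysis, subgroups.** "The consistency of treatment effects on the primary outcome will be explored in predefined subgroups, including age, gender, education". The list continues with implementation stage, tertiles of the baseline site-level rate, blood pressure level and antihypertensive use. All tests are two-sided at 0.05, and the article says the number of tests will be weighed in interpretation.

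**The concern.** The sizing recognises two levels of dependence, site and patient within site, while the stated model carries only the first. With a site intercept alone, two visits by the same patient are treated as no more alike than visits by two different patients at that site.

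For the arm contrast this hardly matters. Arms are allocated by site, and the estimated site variance absorbs the patient-to-patient variation that reaches the site means. A subgroup-by-arm contrast on a patient characteristic draws its information from differences between patients within sites. The site intercept removes the site correlation from that contrast, but the extra likeness of one patient's visits stays in it and is not counted. Standard errors are then too small, and recruiting more sites or patients does not remove the bias.

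What is at stake is the credibility of any statement about which kinds of patient benefit from the decision support system, not the trial's primary conclusion.

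**Working it through.** **Inputs from the article.** 10 sites per arm in stage 1; 50 patients per site; 3 visits per patient; baseline rate 55%; difference 18 points; site correlation 0.05; within-patient correlation 0.1; two-sided 0.05; 90% power. Final trial: 94 sites and 7,656 patients, so 7,656/94 ≈ 81 per site.

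**Step 1: reproduce the stage 1 figure.** Visits per arm: 10 × 50 × 3 = 1,500.

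- Site and patient factors multiplied: (1 + 2 × 0.1) × (1 + 149 × 0.05) = 1.20 × 8.45 = 10.14. Effective visits 1,500/10.14 = 148; power for 55% against 73% is 0.901.
- Site and patient terms nested: 1 + 2 × 0.1 + 49 × 3 × 0.05 = 8.55. Effective visits 175; power 0.943.
- Site term only: 8.45. Effective visits 178; power 0.945.

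Of these, only the version with an extra within-patient factor returns the stated 90%. The within-patient correlation therefore appears to have been used in the sizing.

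**Step 2: variance left out of a patient-level contrast.** For a factor fixed within patient, the true variance divided by the variance from the site-only model is 1 + (v − 1) × r. Here v is visits per patient and r is the same-patient correlation given site. The article does not say whether its 0.1 is a total correlation or is conditional on site, so both readings are shown:

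- total: r = (0.1 − 0.05)/(1 − 0.05) = 0.053
- given site: r = 0.1

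The size of a nominal 5% test is 2 × [1 − Φ(1.96/√factor)].

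| Visits | r | Variance factor | Model SE / true SE | Variance understated by | Actual size |
|---|---|---|---|---|---|
| 3 | 0.053 | 1.105 | 0.951 | 9.5% | 6.2% |
| 3 | 0.1 | 1.20 | 0.913 | 16.7% | 7.4% |
| 4 | 0.053 | 1.158 | 0.929 | 13.6% | 6.9% |
| 4 | 0.1 | 1.30 | 0.877 | 23.1% | 8.6% |

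The understatement is 1 − 1/factor, for example 1 − 1/1.30 = 23.1%. Three visits is the planning figure. Four is the enrolment visit plus quarterly visits over 9 months.

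**Step 3: simulation check.** 94 sites, 81 patients per site, 3 visits, rate 55%, a balanced binary patient factor, no true effect, a site random intercept only on the linear probability scale, 4,000 runs per setting.

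| Total same-patient correlation | Interaction: mean SE / true SD | Interaction: size | Arm contrast: mean SE / true SD | Arm contrast: size |
|---|---|---|---|---|
| 0.10 | 0.952 | 6.5% | 0.992 | 5.6% |
| 0.15 | 0.917 | 7.7% | 0.992 | 5.3% |

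The 0.15 setting corresponds closely to 0.1 given site: (0.15 − 0.05)/0.95 = 0.105. Both rows agree with Step 2, and the arm contrast is nearly untouched.

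**Step 4: sensitivity beyond the article.** At assumed total correlations of 0.3 and 0.5 with 3 visits, the formula gives sizes of 11% and 16%. Simulation with 1,500 runs gave 10.3% and 17.7%. Neither correlation is in the article.

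**The case against.** **The wording is not exclusive.** The article says the models include a site effect; it does not say that this is the only one. A condensed article may leave the full variance specification to an analysis plan that is not shown, and the authors plainly knew of within-patient correlation. This stands in part: a reader might infer that the trial will certainly ignore patient clustering, and the article does not establish that. But it does state a clustering structure for all comparative outcomes, and that structure lacks a level the sizing contains. That is more than an omitted detail.

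**The primary result is safe.** This stands in full. A reader might infer that the main comparison is invalid, but the simulation puts its size at 5.3% to 5.6%.

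**The affected analyses are exploratory.** This also stands, and it limits the importance of the point. Interaction tests are not named explicitly; they are the natural way to examine consistency of effect. The caution about the number of tests addresses multiplicity and does not repair a standard error that is too small.

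**Large error rates are not supported.** Sizes of 11% or more are tempting, since one patient's prescriptions may well resemble each other, but they need correlations the article does not give.

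**The calculation has limits.** The formula applies to factors constant within patient. The article does not say whether blood pressure level and drug use are taken at baseline or per visit; if they vary by visit, these factors do not carry over directly. The simulation used a linear fit, not the planned logistic one.

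**Conclusion.** The point holds in a limited form. The only clustering term named for a visit-level outcome is a site random effect, although the trial is sized with a separate within-patient correlation.

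If the model is fitted as stated, subgroup contrasts on patient-fixed factors have standard errors about 5 to 9% too small at 3 visits and 7 to 12% too small at 4. A nominal 5% test then runs at about 6 to 9%. This rests on the article's own correlations, on 3 to 4 visits per patient, and on no patient-level adjustment being added elsewhere.

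The arm comparison and the two site-level subgroup factors are not materially affected. It is a modest point, worth acting on because the correction costs so little.

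**What to change.** For every visit-level outcome, and explicitly for the subgroup interactions, keep the site random effect and state that standard errors are robust and clustered by site. With 94 sites this is feasible. It allows for dependence among a patient's visits and leaves the effect measure as it is.

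The alternative is a random intercept for patient within site. In a logistic model this changes the odds ratio from site-conditional to patient-conditional. If it is chosen, the effect should be reported on a marginal scale, such as the risk difference, so that the primary effect measure does not change for the sake of exploratory analyses.

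Either way the change is a sentence in the analysis section. It costs slightly wider subgroup intervals and a little more model fitting.

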#### Allocation

Primary care sites selected are randomized to intervention or control arm (1:1 ratio) using computer-generated random numbers stratified by baseline appropriate antihypertensive treatment rate and site characteristics (see detailed stratifying factors for each stage in Supplement 1). Site randomization is performed centrally, and participating sites will be confirmed by local coordinating centers before randomization. The statistician assigns sites to the randomization strata and uses a computer program to randomly allocate half the sites in each strata to the intervention group; the remaining sites are allocated to the control group. Group allocation is unknown to any other team member before a formal announcement to the investigators and sites. Given the nature of the intervention, doctors and participants cannot be blinded. Data analysts will follow a predefined analysis plan to avoid bias.

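### The stated LIGHT model names stage and calendar time but not the factors that stratified site randomisation, so it loses precision to the extent that those factors are prognostic

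*Protocol article*

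**What the plan says.** Allocation, in the LIGHT part of the protocol article, has sites randomised 1:1 "using computer-generated random numbers stratified by baseline appropriate antihypertensive treatment rate and site characteristics", with the factors for each stage listed in Supplement 1. Within each stratum the statistician uses a program to "randomly allocate half the sites in each strata to the intervention group". The arms are therefore balanced by design on the site's own pre-randomisation level of the primary outcome, as grouped for randomisation, and on the chosen site characteristics.

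Statistical analysis, in the same part, sets one model form for all comparative outcomes: a mixed-effects logistic or linear regression "including a random effect for the study site". The adjustment sentence is "Implementation stages will be treated as strata, with adjustment for calendar time to account for secular trends". The baseline site rate is mentioned once more, in the list of subgroups, as "tertiles of baseline cluster-level appropriate treatment rate". No sentence puts the baseline rate or the site characteristics into the main model, and no sentence excludes them.

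**The concern.** The analysis carries the outer layer of the design (stage) into the model but not the layer inside it, within which sites were actually allocated. Stratified allocation makes the arms more alike on the strata and so reduces the true sampling variance of the treatment contrast. A model without those factors does not see this reduction. The random site effect does not recover it, because it counts differences between strata as between-site noise. The reported standard error is then larger than the true one, the intervals are too wide and the test rejects too rarely.

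This matters because between-site variance dominates precision in this trial. Once the number of sites is fixed at 94, extra patients per site add little. Explaining differences between sites is the main lever left, and the trial already holds a natural covariate for it, having used it to randomise.

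**Working it through.** **Inputs from the document.** Control rate and alpha: "the baseline appropriate treatment rate would be 55% with maximum type I error of α = 0.05" (Sample size). Tests are two-sided (Statistical analysis). Also from Sample size: site ICC 0.05, within-patient correlation 0.1, 50 patients per site, 3 visits each, 90% power, 94 sites (47 per arm at 1:1).

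**Assumption.** R² is the share of between-site variance explained by the factors. It is not in the document, so a range from 0 to 50% is shown.

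**Variance factor for a site mean.**

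f = 0.05(1 − R²) + (0.1 − 0.05)/50 + (1 − 0.1)/150 = 0.05(1 − R²) + 0.001 + 0.006

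At R² = 0, f = 0.057. This equals the design effect 1 + 2(0.1) + 49 × 3 × 0.05 = 8.55 divided by 150 visits. The site term is 0.05/0.057, or 88% of it.

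**Standard error of the difference.** SE = √(2 × 0.55 × 0.45 × f / sites per arm).

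**The plan's own figures first.** With 10 sites per arm, SE = √(0.495 × 0.057/10) = 0.0531. The 90%-power detectable difference is 3.2415 × 0.0531 = 17.2 points with normal quantiles and 18.2 points with t quantiles on 18 df, in line with the stated 18. With 47 per arm, SE = √(0.495 × 0.057/47) = 0.0245, which gives 3.2415 × 0.0245 = 7.9 points. The stated 4 points is not reproduced. That is a separate sample-size matter and is not counted here.

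**With the factors in the model** (normal quantiles throughout). Detectable difference = 3.2415 × SE. Power at 4 points = Φ(0.04/SE − 1.96).

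| R² | f | SE | Detectable difference (points) | Power at 4 points |
|---|---|---|---|---|
| 0% | 0.0570 | 0.0245 | 7.9 | 37% |
| 10% | 0.0520 | 0.0234 | 7.6 | 40% |
| 25% | 0.0445 | 0.0216 | 7.0 | 46% |
| 50% | 0.0320 | 0.0184 | 6.0 | 59% |

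Trial status reports 7,656 patients, about 81 per site. With that number the detectable differences are slightly lower, at about 7.7, 7.3–7.4, 6.7–6.8 and 5.7 points; the pattern is the same.

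**With the factors left out.** If the strata balance the explained share exactly, the true SE is the one in the table, but the model reports about 0.0245.

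- True size = 2[1 − Φ(1.96 × 0.0245/SE)]. At 25% this is 2[1 − Φ(2.218)] = 2.7%. At 50% it is 2[1 − Φ(2.616)] = 0.9%.
- Power at 4 points = Φ(0.04/SE − 1.96 × 0.0245/SE). At 25% this is Φ(−0.370) = 36%, against 46% with the factors. At 50% it is Φ(−0.437) = 33%, against 59%.
- Detectable difference = 1.96 × 0.0245 + 1.2816 × SE. At 25% this is 7.6 points, against 7.0. At 50% it is 7.2, against 6.0.

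**Simulation check.** Site means were simulated in 6,000 trials per setting (linear model, about 81 patients per site, assumed 24 strata of 4 sites in 4 stages). The stage-only analysis had type I error of 4.9%, 3.0% and 1.0% at R² = 0, 25% and 50%. Adjusting for the strata gave 4.9%, 5.1% and 4.9%. At 50%, the stage-only model reported a mean SE of 0.0229 against a true 0.0173. Power at 6.5 points was 86% without the strata and 96% with them; at 25% it was 82% and 87%.

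**The case against.** The strongest objection is that the article never calls its list of terms complete. It condenses a fuller protocol, refers to a predefined analysis plan, and sends the stage-specific factors to Supplement 1; neither is shown. A full covariate list often sits in the analysis plan. This stands in part: a reader might infer that the trial has decided to exclude the factors, and the text does not say so. But the section does go down to individual adjustment terms for all comparative outcomes. It names stage and calendar time, and it uses the baseline rate elsewhere. Followed as written, it omits the factors within which sites were allocated.

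The size is also uncertain. If the strata explain nothing, nothing is lost, and at 10% the gain is small. The document does not say whether the ICC of 0.05 is before or after allowing for site characteristics; if after, the gain shrinks. The closed-form sizes of 2.7% and 0.9% hold only for variance that the strata themselves explain. Variation in the baseline rate within a stratum is not balanced by design, so adjusting for it gains precision but leaving it out does not distort the size. All three points stand, which is why the result is a range starting at zero.

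Two stronger readings should be resisted. A reader might infer that the omission biases the result or produces false positives. It does neither: the error is in the conservative direction. A reader might also attribute the gap between the stated 4 points and the recomputed 7.9 to this omission. That gap is present at R² = 0, so it has another cause.

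**Conclusion.** The point holds as a loss of efficiency. Randomisation is stratified by baseline appropriate treatment rate and site characteristics, and the stated model names neither. To the extent that these factors are prognostic, standard errors are too large and power is lost; the treatment contrast stays unbiased and false positives do not increase.

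Over an assumed explained share of 0% to 50%, adjustment corresponds to a detectable difference between 7.9 and 6.0 points. Without it, the true size of the nominal 5% test lies between 5% and roughly 1%, provided the strata themselves carry the explained share. Some loss is likely, since one factor is the site's baseline value of the primary outcome, but the document gives no figure to place it within the range. The numbers are linear approximations to a logistic mixed model. If the unseen analysis plan already includes the factors, the article's model statement is merely incomplete.

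**What to change.** Add a sentence to the LIGHT Statistical analysis section: every LIGHT model includes, as fixed effects, the stratification factors used at randomisation (the site's baseline appropriate treatment rate and the site characteristics used in each stage), alongside stage, calendar time and the random site effect. For the primary outcome, entering the baseline rate as a continuous variable is preferable, because it also captures variation within strata; this is a preference, not a requirement of the design. If the analysis plan already says this, make the two agree.

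Fix the choice before outcome data are analysed, so that adjustment cannot depend on results. The cost is some site-level degrees of freedom out of 94 sites. The exact number depends on the factors in Supplement 1, so check that no stage has too many strata for its sites. No new data are needed, because the factors were already used to allocate the sites.
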